## Methods/design

This is an evaluator-blinded, randomized controlled superiority trial with two parallel groups, and a 1:1 allocation ratio, with an 8-week intervention period and outcomes measured at baseline, 8 weeks and 16 weeks as a follow-up evaluation. The first statistical comparison will be performed after 8 weeks of intervention.

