### Sample size

The sample size will be calculated based on a pilot study with eight patients (four patients in each group) using a multivariate analysis of variance (manova) test with repeated measures, within-between interaction with two groups and two measurements by analyzing calf endurance and the standard deviation of the number of repetitions from the pilot study. A two-tailed alpha error of 0.01 will be considered with a power of 80% considering clinical improvement for subjects with chronic venous disease after the supervised exercise protocol. The effect size will be calculated at the end of the protocol considering the number of repetitions of the calf-endurance test of all study participants. Moreover, considering a 20% loss to follow-up and 5% missing data, the number of participants will be increased by at least 20% based on sample size. The GPower (Germany) version 3.1 program will be used for statistical analysis.

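### At its 20% minimum, the enrolment uplift does not cover the 20% loss and 5% missing data it is meant to offset, and the power that remains depends on two unreconciled alphas

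*Protocol article*

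**What the plan says.** All the sizing statements are in the Sample size section of the protocol article.

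- Error rates: "A two-tailed alpha error of 0.01 will be considered with a power of 80" per cent.
- Planning test: a MANOVA with "repeated measures, within-between interaction with two groups and two measurements", in a design with "two parallel groups, and a 1:1 allocation ratio" (Methods/design).
- Source of the SD: "The sample size will be calculated based on a pilot study with eight patients (four patients in each group").
- Effect size: "The effect size will be calculated at the end of the protocol considering the number of repetitions of the calf-endurance test of all study participants". No required number, SD or target difference is given.
- Attrition, with the assumed losses and the response to them in one sentence: "considering a 20% loss to follow-up and 5% missing data, the number of participants will be increased by at least 20" per cent.

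The statistical paragraph under Data collection, management and analysis sets the significance level at p < 0.05. It analyses the outcomes with a linear mixed model on all available data, without imputation, and includes every randomised participant who has at least one outcome measure.

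**The concern.** The sentence on attrition gives both the expected losses and the allowance for them, and the two do not match. To end with N evaluable participants when a share L is lost, N must be divided by (1 − L). Multiplying by (1 + L) always falls short. Here the multiplier appears to reflect only the 20%, so the 5% is not allowed for at all.

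This section is the only justification for the number enrolled, and calf-muscle endurance is a primary outcome. A team that enrols exactly 20% more than the calculated number follows the plan and yet, if its own loss assumptions come true, has fewer evaluable participants than the calculation requires. A null result could then be read against a power that the stated allowance does not secure.

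**Working it through.** **Inputs.** From Sample size: two-sided alpha 0.01, power 80%, losses of 20% and 5%, minimum uplift 20%, pilot of two groups of four. From the statistical paragraph: p < 0.05. Because no N, SD or effect size is stated, the plan's sample size cannot be reproduced. The effect of attrition on power can still be worked out without them.

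**1. Uplift needed, 1/(1 − L).**

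- 20% loss alone: 1/0.80 = 1.25, an increase of 25%.
- Both losses, compounded: 1/(0.80 × 0.95) = 1/0.76 = 1.316, an increase of 32%.
- Both losses, added: 1/0.75 = 1.333, an increase of 33%.

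**2. What a 20% uplift leaves, f = 1.20 × retention.**

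- 20% loss alone: 1.20 × 0.80 = 0.96.
- Compounded: 1.20 × 0.76 = 0.912.
- Added: 1.20 × 0.75 = 0.90.

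As an illustration with an assumed 60 evaluable participants, the minimum uplift enrols 72, of whom 54 to 55 remain. The losses call for 79 to 80.

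**3. Power at that minimum.** In the normal approximation, power = Φ((z for sizing alpha + 0.842) × √f − z for testing alpha), with z = 2.576 at 0.01 and 1.960 at 0.05. For example, with 0.01 throughout and f = 0.90: 3.418 × 0.949 − 2.576 = 0.666, and Φ(0.666) = 74.7%.

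| f | Sized and tested at 0.01 | Sized and tested at 0.05 | Sized at 0.01, tested at 0.05 |
|---|---|---|---|
| 1.00 | 80.0% | 80.0% | 92.8% |
| 0.96 | 78.0% | 78.4% | 91.7% |
| 0.912 | 75.4% | 76.3% | 90.4% |
| 0.90 | 74.7% | 75.7% | 90.0% |

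A noncentral-t check on the change score at alpha 0.01 (equivalent to the two-by-two interaction) needs an assumed standardised effect. For f of about 0.90 to 0.912 it gives 75.3% to 77.6% for effects of 0.5 to 1.2. At 1.5 it gives 79.3% to 80.1%, because rounding a small N upwards starts that case at 83.7%.

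**4. Precision of the pilot SD.** Two groups of four, pooled, give 6 degrees of freedom. The 95% limits for true SD over pilot SD are √(6/χ²), that is 0.644 and 2.202. The required N scales with the square, so it could be 0.42 to 4.85 times the calculated one. For a target difference fixed in advance and the full calculated N at alpha 0.01:

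- upper limit: Φ(3.418/2.202 − 2.576) = Φ(−1.024) = 15%;
- lower limit: Φ(3.418/0.644 − 2.576) = Φ(2.73), above 99%.

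Averaged over the error in the pilot SD, power is about 69%, with a 58% chance of being under 80%. If N is sized at 0.01 but the test is at 0.05, the same calculation gives a mean of about 83% and a 33% chance of being under 80%.

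**The case against.** **The 20% is a floor.** A reader might infer that the trial has 75% power. The documents do not support that. No number has been fixed, and an uplift of 32% or 33% would satisfy the same wording. The 75% is the power at the least enrolment the plan permits. What remains is that this floor is the only figure given, and it is too low for the losses stated beside it.

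**The final test is declared at p < 0.05.** Sized at 0.01 and tested at 0.05, the trial keeps about 90% power after the same losses. That is a serious objection to any unconditional statement that power is below 80%, and it stands. It does not rescue the uplift: the article does not present the gap between the two alphas as a reserve for attrition, and whichever single alpha is used throughout, the shortfall returns at 75% to 76%.

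**The losses may overlap or be partly recovered.** The plan does not say that the 5% is additional to the 20%. If it lies within it, f is 0.96 and power at alpha 0.01 is 78.0%; the uplift still falls short of the 25% needed. The mixed model on all available data may recover a little, but a participant with only a baseline value says almost nothing directly about the group difference in change. The 75% is therefore close to a lower bound for attrition alone at alpha 0.01.

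**The small pilot is weak practice, not a wrong figure.** Agreed. A reader might also infer that true power averages about 70%, but that figure holds only for testing at 0.01 and for a target difference the plan does not state. A blinded re-check of the SD during recruitment may look like the natural remedy. It would be a new design feature, however, and with recruitment planned from January to May 2020 and an 8-week endpoint, few change scores would be available in time.

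**Conclusion.** The point holds in conditional form. On the protocol's own loss assumptions, the minimum uplift leaves 90% to 91% of the required evaluable number, and it does not cover the 20% loss by itself. This needs no outside figure. The consequence for power is 74.7% to 75.4% with alpha 0.01 throughout, 75.7% to 76.3% with 0.05 throughout, and 90.0% to 90.4% with the mixture that the text currently describes. These results assume exactly 20% uplift, separate losses and no information from lost or missing cases. For power, the conflict between the two alphas matters more than the uplift.

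The pilot SD is supporting context: its limits are wide enough that a single power figure should not stand alone, whichever alpha is chosen.

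**What to change.** 1. In Sample size, replace the increase of at least 20% by division of the required number by 0.75, an increase of at least 33%. If the two losses are meant to compound, divide by 0.76 (32%). Compared with the present minimum this means about 10% to 11% more participants (1.316/1.20 = 1.096; 1.333/1.20 = 1.111). The alternative is to keep 20% and state that power at that minimum is about 75% at alpha 0.01, which costs only a less favourable figure.
2. Reconcile the 0.01 in Sample size with the p < 0.05 in the statistical paragraph, so that the stated power refers to the test that will be used. If 0.05 is chosen throughout and the 20% is kept, the restated power is about 76%. This is a change of text, although the choice of alpha changes the calculated number.
3. When the pilot SD is available, report power as a range over its 95% limits (0.64 to 2.20 times the estimate) for a target difference in repetitions stated in advance. This costs one extra calculation.

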### Data collection, management and analysis

#### Data collection

The baseline and revaluation data will be collected by a trained physical therapist using a protocol for the outcomes related to the questionnaire (VEINES-QOL), demographic data, and CEAP classification. For the physical tests the evaluator will perform a brief orientation, allowing the patient to practice the movement before beginning the test.

A follow-up report will be available to all participants of the IG. It will include evaluation and re-evaluation information for the next medical appointment. The evaluator will refer to the subject’s physician to identify those excluded from the study due to ankle-brachial index (ABI) values below 0.9 [19].

The data will be stored in one of the laboratory computers and double entry will be performed by two study researchers. Access to the data will be limited to the study researchers and any other access must be authorized by the coordinator.

All data collected will be available on the evaluation form and in the proper computer file. Access to these data will be limited only to researchers with prior permission from the study coordinator. The exercise program will be supervised by a physical therapist with expertise in exercise physiology and experience in supervised exercises. All data regarding the treatment protocol will be registered in the subject’s file and attached to the participants’ medical charts.

The statistical analysis will be performed using the GraphPad Prism version 5.0 statistical package software (GraphPad Software Inc., San Diego, CA, USA). The results of patient baseline characteristics and outcome variables (both primary and secondary) will be summarized using descriptive summary measures: expressed as mean (standard deviation) or median (range) for continuous variables and *n* (%) for categorical variables. The sample normality will be tested by the Shapiro-Wilk test. Treatment effects or differences between the study groups for primary and secondary outcomes will be analyzed by linear mixed model for group (usual care versus intervention) and time (baseline, 8 weeks and 12 weeks). As linear mixed models use all available data at each time point, no missing data imputation will be performed. Age and body mass index (BMI) will be included as covariates by adding them to the regression model. The clinical classification CEAP will be included as covariate if randomization imbalance occurs. The analyses will be based on the intention-to-treat principle, including data of all randomized participants with at least one outcome measure. The significance level will be set at 95% (*p* < 0.05). All participants will be included in the analysis of the original groups following the Consolidated Standards of Reporting Trials (CONSORT) recommendations.

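### The primary mixed model does not name the term that carries the treatment effect, although the trial is sized on a group-by-time interaction, and it makes no adjustment for the outcome's baseline value

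*Protocol article*

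**What the plan says.** All references are to the Protocol article.

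- **Data collection, management and analysis, statistical paragraph.** Primary and secondary outcomes are to be "analyzed by linear mixed model for group (usual care versus intervention) and time", and the time factor is given as "time (baseline, 8 weeks and 12 weeks". Baseline is thus a level of the outcome's time factor.
- **Same paragraph, covariates.** "Age and body mass index (BMI) will be included as covariates by adding them to the regression model". CEAP is conditional: "The clinical classification CEAP will be included as covariate if randomization imbalance occurs". The outcome's own baseline value is not listed. Neither a group-by-time term nor a contrast at a particular visit is named.
- **Sample size.** The calculation is for a "within-between interaction with two groups and two measurements", at two-sided alpha 0.01 and 80% power. It does not say which two measurements; baseline and week 8 is a fair inference.
- **Abstract and Methods/design.** The Abstract words the primary outcomes as changes. Both places put the first statistical comparison after 8 weeks.
- **Background.** A further aim is to see whether gains persist after the unsupervised period.
- **Trial design.** Randomisation is stratified by CEAP 2 and 3 versus CEAP 4 to 6.

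**The concern.** The article asks two questions: what the programme does by week 8, and whether the gain lasts. The model paragraph ties neither question to a term in the model. Several candidates could be reported as the treatment effect: the group coefficient, a global interaction test, or a contrast at one visit. They estimate different quantities.

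Two things are at stake. First, a group coefficient taken over all visits includes the pre-treatment visit, where randomisation makes the expected difference zero, and blends week 8 with follow-up. It would understate the week-8 effect and would not be the test on which the trial was sized. Second, if an ordinary interaction is fitted, each arm has its own free baseline mean. The week-8 contrast then becomes a comparison of change scores, which is valid but less precise than a contrast that adjusts for baseline, and the baseline measurement is already being collected.

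**Working it through.** The article gives no sample size, effect size, SD or within-participant correlation, so there is no stated figure to reproduce. The check works in units of the outcome SD. It assumes complete data, equal variances and one correlation rho between any two visits. Rho, the standardised effect d and the share of the gain retained at the last visit (r) are assumptions.

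**1. If the group coefficient is the treatment effect (no interaction).** The coefficient is the mean of the three visit differences. With 0 at baseline, 1 at week 8 and r at follow-up, it is (0 + 1 + r)/3 of the week-8 effect:

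| Gain retained, r | Coefficient as share of week-8 effect |
|---|---|
| 0 | 1/3 = 0.33 |
| 0.5 | 1.5/3 = 0.50 |
| 1 | 2/3 = 0.67 |

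A generalised least squares calculation for the additive model with r = 1 gave 0.667 at rho = 0.3, 0.5, 0.7 and 0.9, so the dilution does not depend on rho.

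*Effect on power, for illustration.* Take d = 0.8, two-sided alpha 0.01 and 80% power. The number per arm is 2(2.576 + 0.842)² × V/d², where V is the variance factor; this is about 36.5 × V. For a baseline-adjusted week-8 contrast, V = 1 − rho²:

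- rho = 0.5: 36.5 × 0.75 = 27.4, so 28 per arm.
- rho = 0.7: 36.5 × 0.51 = 18.6, so 19 per arm.

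At those numbers, with the effect fully sustained, the group coefficient targets 0.8 × 2/3 = 0.533, and its SD factor is √((1 + 2rho)/3):

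- rho = 0.5: SE = 0.816 × √(2/28) = 0.218. Then 0.533/0.218 − 2.576 ≈ −0.13, which is 45% power.
- rho = 0.7: SE = 0.894 × √(2/19) = 0.290. Then 0.533/0.290 − 2.576 ≈ −0.74, which is 23% power.

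**2. If the group-by-time interaction is intended.** The week-8 interaction contrast recovers 1.00 of the week-8 effect at every rho examined, so there is no dilution. With free baseline means it is the difference in mean change, with variance factor 2(1 − rho). Relative to baseline adjustment:

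2(1 − rho)/(1 − rho²) = 2/(1 + rho)

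| rho | Variance ratio | Per arm, change contrast | Per arm, baseline-adjusted |
|---|---|---|---|
| 0.3 | 1.54 | 52 | 34 |
| 0.5 | 1.33 | 37 | 28 |
| 0.7 | 1.18 | 22 | 19 |
| 0.9 | 1.05 | 8 | 7 |

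(Numbers per arm are for d = 0.8, alpha 0.01 and 80% power, before dropout.)

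**3. Is baseline as an outcome itself the fault?** No. With rho = 0.5 and 20 per arm, the SE of the week-8 contrast is:

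- free baseline means: √(2/20 × 1) = 0.316
- one common baseline mean: 0.274
- baseline as covariate: √(2/20 × 0.75) = 0.274

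A common baseline mean gives the same precision as ANCOVA, and the two also agreed at rho = 0.3, 0.7 and 0.9.

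**The case against.** The strongest reply is that the paragraph lists factors and does not declare an additive model. Everything around it points to the interaction: the sample-size test, primary outcomes worded as changes, a first comparison after 8 weeks and a separate question about durability. A reader might infer from the literal wording that the primary analysis is biased towards zero. The documents do not support that. The dilution arises only if the group main effect is the term tested, which the article nowhere says. Nor is the model limited to group and time, since age and BMI are always included and CEAP may be. The Hypotheses section also names no week, so week 8 is inferred as the primary time point from the timing of the first comparison and the sample-size set-up.

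A second reply is that a mixed model with baseline as an outcome is a legitimate analysis and suits an outcome defined as change. That is correct, and in such a model baseline is used, through the change. But under randomisation the change contrast and the baseline-adjusted week-8 contrast target the same group difference, so the wording of the outcome is no reason to prefer the less precise one. The loss does shrink as the correlation rises, and at 0.9 it is only about 5%.

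A third reply is that a journal article may leave model detail to an analysis plan that is not shown. That would answer a complaint about mere brevity. Here the article does state its primary model and covariates, and what it states does not line up with its own sample-size basis.

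**Conclusion.** The point holds as a mismatch and a loss of precision, not as a demonstrated bias. The article plans its size on a group-by-time interaction, then states a model that names no interaction, no week-8 contrast and no baseline adjustment.

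- Read with the group coefficient as the effect, the estimate is 0.33 to 0.67 of the week-8 effect for 0% to 100% retention.
- Read with the interaction, which is the likelier intention, the week-8 contrast is unbiased. Its variance is about 33%, 18% or 5% higher than necessary at correlations of 0.5, 0.7 or 0.9.

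The correlations, the retention pattern and d = 0.8 are assumptions. The dilution fractions rest only on the retention pattern and on balanced, complete visits. The point should be corrected before data are seen, because naming the contrast in advance also removes a later choice among tests.

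**What to change.** State that the treatment effect is the group-by-time contrast at week 8 (primary), and that the contrast at the final follow-up visit answers the durability question. Keep baseline as an outcome, but with one baseline mean common to both groups. This matches ANCOVA precision and keeps every randomised participant with at least one outcome measure, as the intention-to-treat rule in the same paragraph requires.

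An alternative is to model only the post-baseline visits, with the baseline value of that outcome as a covariate. Its small downside is that participants with baseline data alone leave the model, which matters somewhat in a trial that expects 20% loss to follow-up.

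Retain age and BMI. Include the CEAP randomisation stratum whatever imbalance is observed, because it is part of the design and its inclusion should not depend on the data.

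When the time factor is rewritten, reconcile the label of the last visit: the model's levels are "time (baseline, 8 weeks and 12 weeks", while Methods/design has "outcomes measured at baseline, 8 weeks and 16 weeks as a follow-up evaluation".

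The cost is a few sentences of analysis wording. No new data or visits are needed.

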**Methods/design:**

This is an evaluator-blind, randomized clinical trial with an 8-week duration and a follow-up evaluation at week 16. A pilot study with subjects with a CVI diagnosis will be performed to calculate sample size. The participants will be randomly allocated (1:1) into a treatment or a control group (usual care/no intervention). The treatment intervention consists of a bi-weekly supervised exercise program of the lower limbs that will include aerobic training, strengthening and cardiovascular exercises. The participants from both groups will participate in a health education lecture. Primary outcomes are changes in calf-muscle endurance and QOL score. Secondary outcomes are changes in exercise capacity, ankle ROM, electrical muscle activity and cardiac output. The first statistical comparison will be performed after 8 weeks’ intervention.

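### Age and BMI, added as main effects to a mixed model that has baseline among its outcome visits, leave the between-group difference in change essentially unadjusted

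*Protocol article*

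**What the plan says.** All of the following is in the protocol article.

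- **Model** (Data collection, management and analysis, statistical paragraph): a "linear mixed model for group (usual care versus intervention) and time (baseline, 8 weeks and 12 weeks" weeks being the last visit listed. Baseline is therefore an outcome visit and not a covariate. Other sections put the last visit at week 16; that mismatch does not affect this point.
- **Covariates** (same paragraph): "Age and body mass index (BMI) will be included as covariates by adding them to the regression model". Then: "The clinical classification CEAP will be included as covariate if randomization imbalance occurs". No covariate-by-time term is mentioned, and no constraint on baseline means.
- **Effect of interest**: the abstract says "Primary outcomes are changes in calf-muscle endurance and QOL score". The sample size section rests on "repeated measures, within-between interaction with two groups and two measurements". Both indicate the group-by-time difference in change. The statistical paragraph does not name the contrast.
- **Incomplete data**: the analysis set is described as "including data of all randomized participants with at least one outcome measure", with no imputation. The sample size section inflates "considering a 20% loss to follow-up and 5% missing data".

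**The concern.** Age and baseline BMI each take one value per participant. As a main effect, such a covariate shifts the baseline, week-8 and follow-up values of that participant by the same amount. A difference between two visits removes the shift, so a model for change that contains only main effects of age and BMI has nothing left to adjust.

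What is at stake is the meaning of the reported result. The plan commits to these two covariates for every primary and secondary outcome, and the report would describe the treatment effect as adjusted for them. If older or heavier participants respond differently to training and the arms differ by chance in age or BMI, that difference would remain in the estimate while the reader is told that it has been handled. CEAP is to be added only on imbalance, precisely to correct for it. As a main effect it would not correct the difference in change.

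**Working it through.** The plan gives no sample size, effect size or standard deviation (the sample size is to come from an eight-patient pilot), so there is no stated figure to reproduce. The check is algebra, followed by simulation under stated assumptions.

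**1. Algebra, complete data.** For participant i in group G (0 or 1) at visit t:

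Y(i,t) = μ(t) + γG + δ(t)G + β′x(i) + e(i,t), with δ(baseline) = 0 and x = (age, BMI).

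The change to week 8 is

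Y(i,8) − Y(i,0) = [μ(8) − μ(0)] + δ(8)G + [e(i,8) − e(i,0)].

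The term β′x(i) has gone. The likelihood splits into a part for the changes and a part for baseline given the changes. The second part has its own free intercept and group term, so it carries no information on δ(8). The estimate of δ(8) is the difference between arms in mean change, whatever the within-person covariance and whether or not x is in the model.

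**2. Numerical check of step 1.** Generalised least squares was run on 300 random data sets with an arbitrary 3×3 covariance and covariates deliberately imbalanced by arm. Adding the two main effects changed the interaction estimates by at most 2×10⁻¹³ and the standard error by at most 4×10⁻¹⁵, which is rounding error. REML fits (random intercept and unstructured) gave a difference of 0.000000 and a standard error ratio of 1.0000.

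**3. Missing data.** A participant without week 8 has no change to contribute but still supplies a baseline value, so the split in step 1 no longer holds exactly. Assumptions: 20 per arm, total SD about 1, age and BMI together explaining about one third of the variance, 20% or 25% missing at week 8 with some further loss later, and covariate effect on change 0 or −0.2. Main effects against no covariates:

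| Quantity | Result |
|---|---|
| Mean absolute shift of the estimate | 0.02 to 0.05 SD |
| Largest shift in any data set | 0.19 SD |
| Standard error of the contrast | about 0.28 to 0.30 |
| Standard error ratio | 0.989 to 0.993 |

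The effect is small but not nil.

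**4. What would make the covariates act (same assumptions, with and without missing data).**

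| Change to the model | Shift of estimate (mean) | Standard error ratio |
|---|---|---|
| Age×time and BMI×time, covariates do not predict change | 0.05 to 0.06 SD | 1.02 to 1.04 |
| Age×time and BMI×time, covariates predict change | 0.07 to 0.10 SD | 0.97 to 0.99 |
| Baseline means equal between arms, main effects only | 0.06 to 0.09 SD | 0.93 to 0.97 |

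Ratios compare with the same model without covariates.

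**5. Break-even for the interaction terms.** With k = 2 covariates and N = 40, estimating their slopes inflates the variance by about 1 + k/(N − k − 3) = 1 + 2/35 = 1.057. The standard error ratio is √[(1 − R²) × 1.057], where R² is the share of the variance of change that age and BMI explain (assumed; the documents give none).

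- R² = 0: √1.057 = 1.03.
- R² = 0.05: √(0.95 × 1.057) = 1.00.
- R² = 0.20: √(0.80 × 1.057) = 0.92.

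The terms therefore cost about 3% if useless, break even near R² = 5% and gain about 8% at R² = 20%.

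**The case against.** The strongest case against is that the cancellation needs conditions the article does not spell out.

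- **The contrast is not fixed in the statistical paragraph.** It speaks only of treatment effects or group differences, and the Trial design section lists the primary outcomes without the word change. If the contrast were the group difference at week 8, the same main effects would matter: in the simulations they cut the standard error to 0.77 to 0.87 of the unadjusted value and moved the estimate by 0.14 to 0.19 SD. This stands as a limit on the point. The abstract and the sample size section nevertheless both indicate change, and the ambiguity is itself a reason to name the contrast.
- **Covariate-by-time terms are not excluded.** True, and an article condenses. But this is not a case of missing detail: the article states the outcome visits, the covariates and how they enter, and the plain reading is main effects.
- **Data will be incomplete.** "As linear mixed models use all available data at each time point, no missing data imputation will be performed" means that incomplete participants stay in, and the covariates then have a small influence and support the missing-at-random assumption. This stands. A reader might infer that the adjustment does nothing at all; for the data this plan expects, that is too strong.
- **No bias follows.** A reader might infer a biased effect or an inflated type I error. Neither follows: randomisation, stratified by CEAP, protects the unadjusted contrast, and its standard error already allows for chance imbalance.
- **No power loss can be quantified.** A reader might want a power figure. It would need an R² that the documents do not give. It would also need one significance level, whereas the sample size section pairs 80% power with alpha 0.01 and the analysis uses 0.05. None is offered here.

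**Conclusion.** The point holds on the plain reading of the plan: main-effect covariates, baseline as an outcome visit, free group-by-time terms, and difference in change as the effect. Under those conditions age and BMI cancel exactly with complete data. That result rests on no assumed variance or sample size. With 20% to 25% missing at week 8 their influence is about 1% of the standard error and a few hundredths of an SD on average; those figures rest on the simulation assumptions, chiefly 20 per arm. CEAP, if added as a main effect, is in the same position.

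The consequence is a result labelled as adjusted that essentially is not. Validity is not threatened. Any gain in precision from repairing the adjustment is likely to be modest and depends on how far age and BMI predict change, so the case for the repair is that the sponsor's own chosen adjustment should do what it says.

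**What to change.** Amend the statistical paragraph in two steps.

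1. Name the contrast:

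> For each primary outcome the treatment effect is the between-group difference in change from baseline to week 8.

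2. Make the adjustment act on it, by one of:

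> (a) Baseline age and baseline BMI will be included together with their interactions with time.

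> (b) Baseline means will be constrained to be equal between arms, as randomisation justifies, with baseline age and baseline BMI as main effects.

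Treat CEAP in the same way if it is included. Either wording also makes clear that BMI is the baseline value.

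**Cost.** One or two sentences. Option (a) adds four parameters (two covariates × two post-baseline visits) and, at an assumed 20 per arm, can raise the standard error by about 2% to 4% if age and BMI do not predict change; in one complete-data setting at 40 per arm the rise was about 1%. Option (b) adds no covariate parameters and did better in the simulations, but assumes that age and BMI relate to the outcome equally at every visit.
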